### Strategies to improve adherence to interventions {11c}

To improve adherence to intervention protocols, the patient will be instructed to fill out a “patient’s diary” where MFA intake will be documented. This diary is also used to document co-medication, especially TMZ treatment and occurrence of adverse events (AEs). Apart from that, he or she will be requested to bring the empty containers/drug tablets of the MFA to the study visits.

### Relevant concomitant care permitted or prohibited during the trial {11d}

Besides standard TMZ therapy as described above, a prophylactic standard antiemetic regimen using a serotonin antagonist (e.g., ondansetron, tropisetron) prior to administration of standard TMZ is strongly advised. To keep the risk of gastrointestinal ulcers and/or bleeding as low as possible, all trial patients receiving MFA should be treated prophylactically with a proton pump inhibitor. Steroid medication as any other co-medication is performed at the discretion of the local investigator/treating physician. The administration of any other anticancer substance or other anticancer interventions is not permitted. However, it is prohibited to take drugs which can cause health risks when combined with MFA treatment, e.g., lithium or methotrexate. Considering the risk of potentially bleeding gastric ulcers under MFA, antiplatelet (acetylsalicylic acid, clopidogrel) and anticoagulant therapy is not permitted except for low-dose antithrombotic therapy.

### Provisions for post-trial care {30}

In case of progressive or recurrent disease, salvage therapy will be chosen at the discretion of the treating physician. Every subject participating in the trial is insured against any trial-related illness/injuries pursuant to the legal requirements which may occur during the trial. The investigator will inform the subject of the existence of the insurance, including the obligations arising from it.

### Outcomes {12}

In phase I, the primary outcome to be evaluated will be the incidence of DLTs during the first 8 weeks of MFA treatment. DLT for each dose level is defined as any CTCAE5 grade 3/4 organ toxicity or grade 4 hematotoxicity > 2 weeks during the first 8 weeks of MFA treatment; events probably related to the tumor resection and/or perioperative treatment or to the underlying disease are not regarded as DLT. Secondary outcomes in phase I are progression-free survival (PFS) as measured from the inclusion into the trial until diagnosis of progressive disease determined by MRI (according to “response assessment for neurooncology” (RANO) criteria) in the local center, PFS according to post hoc central reference neuroradiological assessment, overall survival (OS) as measured from the day of inclusion into the trial, assessment of safety beyond 8-week MFA treatment, and Karnofsky Performance Score (KPS), Quality of life (QoL), and Mini-Mental State Examination (MMSE) throughout the trial.

In phase II, the primary outcome to be evaluated will be PFS (randomization until the diagnosis of progressive disease according to RANO criteria). Secondary outcomes will be OS (randomization until death), continuous monitoring of AE/severe adverse events (SAE)/suspected unexpected serious adverse reactions (SUSARs), and quality of life throughout the trial (measured by KPS, QoLs, and MMSE). Survival analyses also include patients from phase I who received MFA at the same dose as applied in phase II.

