### Intervention description {11a}

In phase I, there is one treatment arm and a dose-finding algorithm will be performed as described in the following. The participants will receive standard TMZ therapy for eight cycles (TMZ application orally on day 1–5 in a 28-day cycle, dose 150–200 mg/m^2^ body surface). In addition to that, the first three patients will receive 2 × 100 mg/day MFA daily (see also Fig. 1 dose-finding scheme). If no DLT occurs, the next three patients will be treated with 2 × 200 mg/day. Again, if no DLT occurs, this dose will be used for phase II. In both steps, if 1/3 patients develop a DLT, another three patients will be included. If there is a DLT in 1/6 patients, the dose will be elevated or the 2 × 200 mg/day dose will be used for phase II. If > 1 DLTs occur, the dose will be reduced in a next step to 2 × 50 mg/day and the same algorithm will be applied. If there are > 1 DLTs in 6 patients and the lowest dose of 2 × 50 mg/day, phase II will not be initialized. DLT is determined in the first 2 courses of MFA (within 8 weeks/56 (±3) days after first study treatment administration) in subjects with a compliance rate of 90% (i.e., 50 days of treatment) and no overdose. If judged to be related to the administration of MFA, the following toxicities will be considered a DLT: grade ≥ 4 hematotoxicity for > 14 days in courses 1 and 2; grade ≥ 3 for any other organ toxicity.

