### Methods in analysis to handle protocol non-adherence and any statistical methods to handle missing data {20c}

In phase I, patients who are not evaluable for DLT will be replaced. A patient is evaluable for DLT if the DMSB has determined that a DLT has occurred in this patient during the first 56 days after treatment start (independent of the duration of MFA intake) or if until DLT visit (day 56 ± 3 days after start of MFA treatment) the patient has taken at least 100 doses of MFA (i.e., 89.3% of the maximally positive cumulative dose in 56 days) as documented by the patient’s diary and the documented return of 1 empty container of MFA (containing 100 capsules) (for dose step 2 × 100 mg daily or 2 × 50 mg daily) or of 2 empty containers of MFA (for dose step 2 × 200 mg daily).

In phase II, subjects dropping out of the trial prior to randomization will be listed as screening failures including the reason for dropout. Subjects prematurely discontinuing the trial will be censored regarding the analysis of PFS or OS at the time of discontinuation. Subjects dropping out after randomization will be analyzed using all available data and will not be replaced. The technique for the analysis of missing values will be defined in the statistical analysis plan. A check of a possible treatment effect on the frequency of missing values will be performed.

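### The phase I DLT is defined in two ways that differ on the top grade and on attribution, and neither says how hematotoxicity fatal within 14 days is counted

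*Protocol article*

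**What the plan says.** Four sections bear on what counts as a DLT.

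- **Outcomes {12}** makes DLT incidence in the first 8 weeks the phase I primary outcome. It defines a DLT as "any CTCAE5 grade 3/4 organ toxicity or grade 4 hematotoxicity > 2 weeks during the first 8 weeks of MFA treatment". Attribution works by exclusion only: "events probably related to the tumor resection and/or perioperative treatment or to the underlying disease are not regarded as DLT".
- **Intervention description {11a}** contains the dose-finding rule and its own definition: "If judged to be related to the administration of MFA, the following toxicities will be considered a DLT", namely "grade ≥ 4 hematotoxicity for > 14 days in courses 1 and 2; grade ≥ 3 for any other organ toxicity". It also sets the cohort rule: "In both steps, if 1/3 patients develop a DLT, another three patients will be included". With no DLT in three, or one in six, the step is passed.
- **Criteria for discontinuing {11b}** stops MFA for related organ toxicity of grade 3 or higher, with an exception for asymptomatic grade 3 laboratory changes that neither DLT definition contains. For hematotoxicity it names grade 4 for more than 14 days.
- **Section {20c}**, on non-adherence and missing data, states: "In phase I, patients who are not evaluable for DLT will be replaced". There are two routes to being evaluable. Either the "DMSB has determined that a DLT has occurred in this patient during the first 56 days after treatment start", whatever the MFA intake, or "the patient has taken at least 100 doses of MFA (i.e., 89.3% of the maximally positive cumulative dose in 56 days" by the DLT visit.

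**The concern.** DLT incidence is the phase I primary outcome and the only quantity in the escalation rule, so it needs one definition. The article gives two, and they differ in both directions. Section {12} is narrower at the top of the grade scale, because it stops at grade 4. It is wider on attribution, because it does not require a relation to MFA. A separate gap is common to both: the duration condition on hematotoxicity has no provision for a patient who dies before it is met.

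The evaluability rule adds to this. A death that is not classed as a DLT is not simply recorded elsewhere. Depending on how many doses were taken, the patient either leaves the cohort and is replaced or stays in it as a patient without a DLT. With cohorts of three, one such patient separates passing the step from adding three more patients.

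**Working it through.** **1. The plan's own figure.** Two doses a day for 56 days is 2 × 56 = 112 doses, and 100/112 = 89.3%, as section {20c} states. At full intake the 100th dose falls on day 100/2 = 50.

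**2. The definitions side by side.** Grade 5 is taken to mean death, as is standard in CTCAE; the article does not spell this out.

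| Event in the first 56 days | {11a} | {12} |
|---|---|---|
| Grade 5 organ toxicity, related to MFA | DLT | Not named; a DLT only if an earlier grade 3 or 4 phase is counted |
| Grade 3 or 4 organ toxicity, not related to MFA and not due to surgery, perioperative care or disease | Not a DLT | DLT |
| Grade 4 hematotoxicity > 14 days, related to MFA, then death | DLT | DLT |
| Hematotoxicity fatal before the > 14-day condition is met | Not met | Not met |

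Rows 1 and 2 are conflicts between the sections. Row 4 is a gap in both, so aligning the grade ranges alone would not close it.

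**3. What section {20c} does with a toxic death not classed as a DLT.**

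- Fewer than 100 doses (about days 1 to 49): neither route to evaluability is met, and the patient is replaced.
- 100 or more doses (about days 50 to 56): the intake condition is met, and the patient can be counted as evaluable without a DLT.
- In both cases the result changes if the monitoring board determines a DLT.

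**4. Effect on one cohort.** Suppose one early toxic death occurs and the other patients have no DLT. If the death counts, the cohort is 1/3 and three patients are added. If that patient is replaced by one without a DLT, or kept as a non-DLT, the cohort is 0/3 and the step is passed.

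**5. Effect on the chance of passing a dose step.** Let *p* be the rate of non-fatal DLT and *q* the rate of fatal toxicity that the wording leaves uncounted. Neither rate is in the documents; both are assumed. With DLT probability *d* per evaluable patient, the {11a} rule gives

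P(pass) = (1 − d)³ + 3d(1 − d)² × (1 − d)³,

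with d = p + q if deaths count, d = p/(1 − q) if those patients are replaced, and d = p if they are kept as non-DLT.

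For p = 0.10 and q = 0.05:

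- counted, d = 0.15: 0.614 + 0.200 = 0.81
- replaced, d = 0.10/0.95 = 0.105: 0.716 + 0.181 = 0.90
- kept, d = 0.10: 0.729 + 0.177 = 0.91

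| Assumed p, q | Counted | Replaced | Kept as non-DLT |
|---|---|---|---|
| 0.05, 0.02 | 0.95 | 0.97 | 0.97 |
| 0.10, 0.05 | 0.81 | 0.90 | 0.91 |
| 0.20, 0.10 | 0.49 | 0.66 | 0.71 |

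**The case against.** The strongest reply is that escalation is decided in {11a}, beside a definition with no upper limit on grade, and that {11b} is also open-ended for organ toxicity. On that view the grade 3/4 in {12} is shorthand. This stands in part: an MFA-related fatal organ toxicity is a DLT where the dose decision is described. It does not remove the conflict, because {12} is the section that formally defines the primary outcome. Nor does it help with early fatal hematotoxicity, which {11a} also misses.

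A reader might infer that any treatment-related death falls outside the DLT count and that the patient is then always replaced. The documents do not support that, for four reasons.

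- Hematotoxicity of grade 4 that lasts more than 14 days and then proves fatal meets both definitions.
- An organ toxicity that passed through grade 3 or 4 before death arguably meets {12}. A fatal bleed caused by a cytopenia might be classed as organ toxicity, which carries no duration condition.
- Replacement requires fewer than 100 doses and no DLT determination by the board. The board route exists so that early toxicity is not lost to the intake rule.
- The board reviews DLT data after each dose step and can meet at any time ({21a}). Serious events are reported at once and assessed a second time by the sponsor ({22}).

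These safeguards make it unlikely that a toxic death would pass unnoticed. They do not say which definition the board applies when it determines a DLT, and the article supplies two.

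**Conclusion.** The point holds as a contradiction in a stated primary-outcome rule, together with one narrow gap. Sections {11a} and {12} disagree on the upper grade and on attribution. Hematotoxicity fatal before the 14-day condition is met satisfies neither. Through {20c}, a death left unclassified could drop out of a 0/3 versus 1/3 decision, by replacement before about day 50 or by being kept as a non-DLT after that, unless the board determines a DLT.

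The size depends on rates that the documents do not give. Over the assumed range, leaving such deaths uncounted raises the chance of passing a dose step from 0.95 to 0.97 at the low end and from 0.49 to 0.66–0.71 at the high end. These figures assume that every death in *q* goes uncounted, so they are the outer effect of the literal wording and not a forecast. The attribution mismatch does not depend on deaths at all: it affects ordinary grade 3 and 4 events.

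**What to change.** Reconcile {11a}, {11b}, {12} and {20c} to a single DLT definition with one grade range and one attribution rule, stated once and cross-referenced elsewhere. In the same place the sponsor should state how a toxicity-related death in the first 56 days, including hematotoxicity fatal within 14 days, enters the DLT count and the evaluability rule. It should also say whether an event is graded at its worst or at any grade reached. Which clinical rule is right is for the sponsor and the monitoring board; this review does not choose one.

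The cost is a few lines of wording. The cohort sizes and schedule stay as they are. A listing of deaths in the first 56 days by dose level, replaced patients included, would be a useful addition to the phase I interim report described in {21b}, but it is optional and the point does not rest on it.

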### Participant timeline {13}

The participant timeline is illustrated in Fig. 2 and the extent of the visits is summarized in Table 1.

**Fig. 2 Fig2:**
[figure not shown]
Timeline of visit and assessments

**Table 1 Tab1:**
[figure not shown]
Visits and assessments in the MecMeth/NOA-24 trial

*DLT visit will only be performed in phase I. In phase I, visit 2.3 is only performed additionally; if the start of cycle 3 is prolonged for more than 3 days after the DLT visit, all patients in phase II have visit 2.3

**EoT: end of treatment is reached 3 days after last MFA intake (phase I and experimental arm of phase II) or on day 31 of the last TMZ cycle (standard arm of phase II)

***End of study and of follow-up in the entire trial will be reached when *both* of the following requirements are fulfilled: (1) at least 6 months after randomization of the last patient in phase II *and* (2) at least 3 days after definite termination of MFA intake in the last patient receiving MFA therapy (i.e., all patients have concluded study-related MFA intake for more than 3 days)

^1^Every 8 weeks: progression assessment, Karnofsky score and QoL, blood samples

^2^Na, K, creatinine, ASAT, ALAT, bilirubin

^3^Gadolinium-enhanced MRI obtained prior to inclusion/randomization can be used as baseline MRI if the interval between this MRI and the start of study therapy is shorter than 21 days. In patients who have undergone re-resection prior to randomization (only possible in phase II), the MRI used as baseline MRI has to be a postoperative MRI

^4^Relapse tumor resection 7–10 days after initiation of study therapy, tissue asservation should take place 2–4 h after the last intake of MFA/TMZ: (1) fresh frozen, (2) 4% PFA, and (3) FFPE tumor material for MFA/MFA metabolite level determination and for analysis of MFA-dependent tissue effects. The exact timepoint of the last MFA intake prior to resection and the exact timepoint of asservation of the tumor material have to be documented

^5^Timepoints (to be documented): (a) 2 h after first intake, (b) on the days between MFA start and resection daily blood sampling 2 h after morning application of MFA (optional), and (c) on the day of resection 5 blood samples at an interval of 2 h (0 h (prior to last preOP MFA dose) 2 h, 4 h, 6 h, 8 h later)

^6^Only at the first follow-up visit after discontinuation of MFA

^7^Only during ongoing MFA treatment + 3 days

^8^Only if clinically indicated

Briefly, patients start therapy within 7 days after inclusion/baseline visit. If according to the local treating neurosurgeon and the local neurooncological tumor board, re-resection of the tumor is clinically indicated and can be safely deferred until day 7–10 after initiation of MFA/TMZ therapy, tumor resection is performed 7–10 days after initiation of therapy. This is mandatory in phase I and optional in phase II. Resected tumor tissue is used for translational analyses of intratumoral MFA/MFA metabolite levels and detection of cellular and molecular effects of MFA. Also, blood analyses are performed for the determination of MFA blood levels 2 h after the first intake of MFA on day 1 and at 5 timepoints on the day of resection. During therapy, further visits are scheduled every 4 weeks prior to the start of a new TMZ cycle. These visits include clinical and standard laboratory examinations, documentation of co-medication documentation of (S)AE, KPS, and, every 8 weeks, contrast-enhanced MRI and QoL evaluation. In phase I, DLT evaluation is added at the visits prior to cycle 2 (day 28 ± 3) and cycle 3 (day 56 ± 3). MFA/TMZ treatment ends after 8 4-week cycles, at progression, or if MFA or at the timepoint when MFA or TMZ treatment has to be prematurely discontinued for whatever reason, e.g., intolerable toxicity, whatever comes first. After the end of the study therapy, patients are followed with clinical examination, contrast-enhanced MRI, and documentation of KPS, QoL, and further tumor therapy every 8 weeks. End of study and of follow-up in the entire trial will be reached when both of the following requirements are fulfilled: (1) at least 6 months after randomization of the last patient in phase II and (2) at least 3 days after definite termination of MFA intake in the last patient receiving MFA therapy (i.e., all patients have concluded study-related MFA intake for more than 3 days).

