### Trial design {8}

The study consists of a single-arm phase I part and a randomized, parallel-group, and unblinded phase II part.

In phase I, patients with the first relapse of MGMT-methylated glioblastoma are screened for the trial. After inclusion, patients are pretreated with MFA in addition to standard TMZ and tumor resection will be performed 7–10 days after initiation of therapy. MFA tissue level measurements and translational analyses are performed on the tumor material obtained from resection. Each patient is particularly screened for dose-limiting toxicities (DLTs) during the first 8 weeks of his/her MFA treatment. Patients are recruited in two cohorts of three to six patients. Dose adaptation in between cohorts depends on the occurrence of DLTs as described below.

All patients of phase I are followed for toxicity and efficacy until the end of phase II.

In phase II, patients with the first relapse of MGMT-methylated glioblastoma are screened for the trial. After inclusion, patients are randomized (1:1) into two parallel groups, the experimental or the standard treatment arm. The experimental treatment is defined as treatment with MFA (dose determined in phase I) in addition to standard TMZ. The standard treatment arm is defined as monotherapy with TMZ (150–200 mg/m^2^ body surface). If tumor resection for the relapsed tumor is clinically indicated, the local treating neurosurgeon can decide whether the resection can be safely postponed until day 7–10 after initiation of therapy (optional, not a prerequisite for study participation in phase II) and tumor material for determination of MFA levels can be obtained.

MFA is taken at the dose determined in phase I. Daily MFA treatment is continued for 8 4-week courses (i.e., 224 days), until tumor progression, until the occurrence of a DLT attributable to MFA, or until definitive discontinuation of standard TMZ, whatever comes first. In case MFA therapy is terminated, standard TMZ therapy can be continued at the discretion of the treating physician.

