### Sample size {14}

Phase I uses an adaptive design based on DLTs (see Fig. 1). Starting with 3(-6) patients per dose level is standard for dose finding in phase I. Starting with a middle-level MFA dose of 2 × 100 mg/day (according to the US registration of MFA) ensures that only two dose levels have to be explored (*n* = 6–12 patients). Patients not evaluable for DLT or MFA tumor levels will be replaced (conservative estimate, 1/6 patients; thus maximal patient number in phase I, 12 + 2 = 14).

The randomized phase II part accrues 30 patients per arm. For the evaluation of PFS, the experimental arm also includes the 3–6 patients of phase I which have been treated with the same dose of MFA as in phase II for an additional analysis. Since phase II is searching for indications of efficacy but is not a confirmatory trial, dropouts will not be replaced. In glioblastoma trials, the dropout rate is relatively low (e.g., 9% in CeTeG/NOA-09 trial). Therefore, and since data from dropout patients are included as censored observation, the results may be expected to be robust regarding patients with short follow-up/early dropouts.

With 30 subjects per arm and a two-sided alpha level of 10%, we could detect a hazard ratio of approximately 0.44 if we assume a PFS-6 of 40% for the reference treatment and use a power of 80%.

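### Progression MRIs in phase II are attached to TMZ cycle visits rather than to calendar time from randomization, so unequal TMZ delay between arms can bias PFS slightly, in either direction

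*Protocol article*

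**What the plan says.** **During therapy.** In Participant timeline {13}, "During therapy, further visits are scheduled every 4 weeks prior to the start of a new TMZ cycle". The next sentence lists what these visits contain, including contrast-enhanced MRI every 8 weeks.

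**Cycle delay.** The discontinuation criteria {11b} stop MFA only once a TMZ delay exceeds 8 weeks from the start of the previous course, so shorter delays remain on study. Statistical methods {20a} plans to describe TMZ delays in later courses.

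**After therapy.** MRI continues every 8 weeks once study therapy has ended. A Table 1 footnote defines the end of treatment separately by arm: "end of treatment is reached 3 days after last MFA intake (phase I and experimental arm of phase II) or on day 31". The day-31 rule is for standard-arm patients and counts from the start of their final TMZ cycle.

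**Endpoint.** Phase II PFS runs from randomization to the diagnosis of progression by MRI at the local center {20a}. Patients and care providers are not blinded {17a}. The blinded neuroradiological reading is a post hoc re-analysis of MRIs already taken.

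The text at hand gives no phase II MRI schedule counted from randomization and no MRI window. The bodies of Table 1 and Fig. 2 are not shown.

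**The concern.** Progression found on MRI is dated by the scan that shows it. The comparison of PFS is fair only if both arms are scanned on the same dates after randomization. Here the scan belongs to a visit that precedes a TMZ cycle, and cycles may start late. Both arms receive TMZ, but only one also receives MFA. If MFA changes how often cycles are delayed, one arm is scanned later and appears to progress later, even if the drug does nothing.

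The blinded central reading does not repair this, because it uses the same scans. The trial looks for first signs of efficacy in 60 patients at a two-sided 10% level, so an avoidable shift in the false-positive rate is worth removing if the remedy is cheap.

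**Working it through.** **1. The plan's own figure.** Sample size {14} states: "With 30 subjects per arm and a two-sided alpha level of 10"%, "we could detect a hazard ratio of approximately 0.44", assuming "a PFS-6 of 40% for the reference treatment and use a power of 80"%. Allocation is 1:1.

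- z values: 1.645 + 0.842 = 2.487; squared, 6.18.
- Schoenfeld events: 4 × 6.18 / (ln 0.44)² = 24.73 / 0.674 = 36.7, so 37.
- Freedman events: 6.18 × (1.44 / 0.56)² = 40.9, so 41.
- Control hazard, exponential: −ln(0.40) / 6 = 0.153 per month; median 0.693 / 0.153 = 4.54 months.
- The phase II accrual period is not stated. With 6 months' minimum follow-up, no dropout and assumed uniform accrual, the detectable HR is 0.439 (Freedman, 12 months' accrual) or 0.434 (Schoenfeld, 6 months). Over 0-30 months' accrual it ranges from 0.35 to 0.49.

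The stated 0.44 is reproducible and is not in question.

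**2. How far a cycle can slip.** 8 weeks from the previous start is 56 days; 56 − 28 = 28 days beyond a normal cycle.

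**3. End-of-treatment dates without delay.** MFA arm: 224 + 3 = day 227. Standard arm: seven full cycles plus day 31 of the eighth, 7 × 28 + 31 = day 227. They coincide.

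**4. Bounding case: one whole arm late.** Simulation with true HR 1, exponential PFS, 30 per arm and progression recorded at the next scan (± 3 days). Accrual of 24 months (assumed) plus 6 months' follow-up; two-sided 10% log-rank test; 5,000 runs; control PFS-6 40%.

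| Delay per 8-week block | MFA arm only late: HR | Favours MFA | Control arm only late: HR | Favours MFA |
|---|---|---|---|---|
| none | 1.00 | 5.6% | – | – |
| 3.5 days | 0.90 | 10.5% | 1.12 | 2.2% |
| 7 days | 0.93 | 8.8% | 1.09 | 3.0% |
| 14 days | 0.94 | 7.5% | 1.06 | 3.1% |
| 28 days | 0.91 | 9.2% | 1.09 | 3.0% |

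With the 3-month median PFS from the Background, the MFA-only rows become HR 0.84-0.89 and 11-15%, and the control-only rows HR 1.12-1.18. An equal 7-day delay in both arms gives HR 0.99. The effect does not grow steadily with delay, probably because a log-rank test reacts to the order of nearly simultaneous scan dates.

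**5. Partial delay in both arms (all rates assumed).**

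| Cycles delayed, control v MFA | Delay | Setting | HR | Favours MFA |
|---|---|---|---|---|
| 15% v 15% | 5-14 days | PFS-6 40% or 3-month median | 0.99-1.00 | – |
| 15% v 30-45% | 5-14 days | PFS-6 40% | 0.95-0.97 | 6.5-8.3% |
| 15% v 30-45% | 5-14 days | 3-month median | 0.93-0.95 | 7.6-8.9% |
| 10% v 20%, 15% v 30%, 20% v 30% or 40% | 7 days (also 14 at 15% v 30%) | scan jitter ± 3 or ± 7 days | 0.95-0.98 | 5.8-7.2% (5.5-5.7% with no delay) |

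The first three rows use 18 months' accrual and 2,500 runs per scenario, so the simulation error on a 7% rate is √(0.07 × 0.93 / 2500) = 0.5 percentage points. Putting more delay in control reverses the bias.

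**6. End-of-treatment rule alone.** With equal TMZ delay and only the end-of-treatment date differing by arm, HR is 0.98 (5.8-6.6% favour MFA). Early MFA stop in 10-30% of the MFA arm, with the scan clock restarted, gives 0.99-1.00.

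**7. At the design effect.** With true HR 0.44 and only the MFA arm late, the mean estimate moves from 0.42 to 0.39-0.41.

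**The case against.** The strongest reply is that the article condenses the schedule. Table 1 and Fig. 2 may fix MRI days and windows. The stated interval is 8 weeks in both arms, one footnote gives 8-weekly progression assessment without mentioning cycles, and no sentence says that an MRI is postponed when TMZ is. This stands as far as it goes: a site that reads the interval as calendar time introduces no bias. But the sentence that places the MRI puts it inside cycle-linked visits, so the other reading is at least as natural. The point rests on that wording, not on something missing.

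Three stronger readings are tempting and are not supported:

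- **That a footnote shows phase II scans moving with the cycle.** The clause "if the start of cycle 3 is prolonged for more than 3 days after the DLT visit" decides when a phase I patient has an additional visit. It does not mention MRI, and phase I lies outside the randomized comparison.
- **That the arm-specific end-of-treatment date is an equal second cause.** The two dates coincide at day 227 without delay. A restart of the 8-week clock at that date is inferred, not stated, and the effect is small.
- **That PFS will be biased towards MFA, by about 10%.** This needs delay throughout the MFA arm and none in control, although both arms receive TMZ. No section gives a delay rate or says that MFA raises it, so the direction is open.

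It is also fair that phase II is declared non-confirmatory and that TMZ delays will be described. Description would reveal unequal delay, but it would not restore comparable scan dates.

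**Conclusion.** The point holds as a cheap improvement, not as a serious flaw. As written, scan dates can differ by arm in an open-label PFS comparison. Under partial delays in both arms with more in the MFA arm, the null HR moves to about 0.93-0.98. The one-sided false-positive rate rises from 5% to about 6-8%, with 8.9% the highest value in the partial-delay runs. More delay in control produces the opposite bias, and equal delay produces essentially none. The end-of-treatment definition contributes an HR shift of 0.02 or less.

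These sizes rest on assumed delay rates and lengths, an assumed accrual period, exponential PFS, and scans that follow the cycle. Against a target HR of 0.44 the bias is small.

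**What to change.** In Participant timeline {13} and Table 1, state that phase II response MRIs are done every 8 weeks by calendar time from randomization, with one stated window, identically in both arms. This should apply until progression, regardless of TMZ cycle delay, MFA stop or the end-of-treatment visit. Tabulate actual scan intervals by arm in the report.

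With the same calendar schedule in both arms, the simulated null HR is 0.99-1.00 and the test favours MFA in 5.0-5.6% of runs. Sample size and detectable HR do not change, and the number of scans is essentially the same. The downside is an occasional separate MRI appointment when a cycle is delayed.
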